### Trial design {8}

An outline of the trial design and sample size is summarized in Table 1. This study is a cluster-randomized controlled trial (cRCT) with 30 clusters per treatment arm (SR and placebo), consisting of 4 months of baseline data collection and after baseline, two independent cohorts enrolled (cohort 1 and cohort 2) and each followed for 12 months for a total of a 24-month follow-up with intervention.

**Table 1 Tab1:** Outline of the cluster design and sample size for the SR cRCT in Busia County, Kenya

Cluster design	Baseline cohort	Intervention cohorts		
	4-month follow-up (*n* = 2040)	Time of intervention deployment	12-month follow-up (cohort 1) (*n* = 2040)	12-month follow-up (cohort 2) (*n* = 2040)
**Core area** 60 clusters total	20 subjects per cluster 1200 subjects total	Year 1	SR (30 clusters), Placebo (30 clusters) 14 subjects per cluster 840 subjects total	n/a
		Year 2	n/a	SR (30 clusters), Placebo (30 clusters) 14 subjects per cluster 840 subjects total
**Buffer zone** 60 clusters total	14 subjects per cluster 840 subjects total	Year 1	SR (30 clusters), Placebo (30 clusters) 20 subjects per cluster 1200 subjects total	n/a
		Year 2	n/a	SR (30 clusters), Placebo (30 clusters) 20 subjects per cluster 1200 subjects total

For the evaluation of the primary epidemiological objective (PE), a total of 28 subjects (HHs) will be recruited from each core area of a cluster or equivalently 14 subjects (HHs) per cohort per cluster (factoring in a 35% loss-to-follow-up (LTFU) rate). For the evaluation of the secondary epidemiological objective on SR diversionary effect, a total of 40 subjects (HHs) or equivalently 20 subjects (HHs) per cohort per cluster will be recruited from each buffer zone (factoring in a 35% LTFU rate). At least one child aged ≥ 6 months old to 9 years and 11 months old from each HH will be recruited for biweekly (every 2 weeks) malaria check-ups during the follow-up period with intervention.

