### Outcomes {12}

The primary outcome measure of this cRCT will be the first-time malaria incidence rate as measured by microscopy in children aged ≥ 6 months to 10 years.

Secondary outcome measures include:
Overall new *Plasmodium falciparum* malaria infections, as measured by microscopy;The first-time and overall *P. falciparum* malaria infections in buffer zones, as measured by microscopy;The first-time and overall *P. falciparum* malaria infections by two age groups (≤ 59 months old; 5 years old to 9 years and 11 months old), as measured by microscopy;Anopheline-human contact (indoor and outdoor) using human biting rate (HBR) as an indicator for all anophelines and by anopheline species, as measured by HLC during 12-h intervals on a quarterly basis;Anopheline survival and population age structure using parity rate as an indicator for all anopheline and by anopheline species, as measured by mosquito ovarian dissections from a sub-sample of anophelines collected during HLC procedures;Anopheline infectivity using sporozoite rate as an indicator for all anopheline and by anopheline species, as measured by laboratory detection of sporozoites in mosquito heads and thoraces from a sub-sample of anophelines collected during HLC and/or CDC light trap collections;Entomological inoculation rate (EIR) as an indicator of transmission intensity for all anophelines and by anopheline species, as measured by calculating the number of sporozoite-infected anopheline mosquitoes captured per person from CDC light trap and/or HLC collections;CDC light trap indoor density for all anophelines and by anopheline species, as measured by light trap collections during 12-h intervals on a monthly basis;Insecticide resistance, as measured by WHO filter paper test and CDC bottle assays during baseline and intervention phase.Adverse events (AEs) and serious adverse events (SAEs), as measured by solicited and unsolicited reports during baseline and intervention phase. Mean, minimum, and maximum frequency and percentage of AEs and SAEs across clusters among enrolled subjects will be summarized by treatment arm.

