#### Cohort follow-up

Children enrolled in the baseline cohort will be followed for a 4-month period, prior to the distribution of the study products. To avoid substantial LTFU due to study fatigue, two independent cohorts (cohort 1 and cohort 2) will be recruited and followed with intervention each for 12 months (see Trial Design {8}); therefore, the total period of follow-up will be 28 months; 4-month baseline phase and 24 months after deployment of the intervention. Cohort 1 will end 12 months after the SR is deployed. Cohort 2 will be recruited, enrolled, and cleared of infection with a treatment dose of AL at enrolment as described above. Children enrolled in the baseline cohort will be eligible for inclusion in cohorts 1 or 2; however, those children enrolled in cohort 1 during intervention will not be eligible for inclusion in cohort 2. The recruitment, enrolment, screening, and follow-up of cohort 2 will be the same as described for the cohort 1.

Follow-up visits for each baseline, cohort 1, and cohort 2 will alternate between a clinic visit (monthly; passive case detection) and a home visit (every 2 weeks; active case detection). Routine blood sampling will occur at the clinic, whereas blood sampling will only occur during home visits if subjects have reported history of fever in the last 48 h. Study participants will be issued with an appointment card where all upcoming appointments will be recorded. In between the clinic appointments, community interviewers may refer participants to the clinic for additional assessment by the clinical officer using the participant referral slip. Participants will be instructed to visit a study health facility for any unscheduled sick visits, or they will be visited at their home if they cannot reach the clinic. Missed visits will be considered minor protocol deviations and will be collated and reported to KEMRI Scientific Ethical Review Unit (SERU) and UND along with the annual progress report. Three consecutive missed visits will prompt consideration for LTFU and withdrawal from the study.

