### Adverse event reporting and harms {22}

The SR product contains transfluthrin, a chemical used in currently available HH mosquito control products such as mosquito coils. Exposure to the product may cause mild eye and skin irritation. These effects are usually transient and disappear after time. The product may be harmful if chewed on or swallowed, so HH owners will be advised to keep it away from children. The SR product will be fixed at a position that is out of the reach of children and it will be monitored at replacement to ensure it has not been moved. If a product is found to have been removed from its position in the HH, study staff will discuss with the HH owner to determine why it was removed and if there was any problem that led to its removal. Study staff will also reiterate safety precautions that should be taken in regard to the SR product.

AEs and SAEs of interest will be collected through passive surveillance by CHVs on children enrolled in the cohort and on other HH members who receive the study product. Additionally, AE and SAEs of interest will be solicited from study participants during follow-up visits (every 2 weeks) either in the house or clinic. We will also rely on passive surveillance of the outpatient registers at the local health facilities for reports of AE/SAE. Additionally, we may also collect unsolicited reports during compound visits and/or product replacement. Anyone experiencing the SAEs or AEs of interest will be encouraged to seek care for at the study clinic where our clinical staff will attend to them at no cost.

Unexpected SAEs affecting the cohort participants determined to be at least “possibly related” will be reported to the KEMRI SERU, study sponsor at UND, and Independent DSMB within 24 h of the PI becoming aware of the SAE. The initial report will be a short description by email, which will be followed within 7 days by a more detailed description of the SAE. AEs of interest considered at least “possibly related” will be reported to the same groups on at least an annual basis.

An AE or suspected AE is considered “serious” if it meets the following conditions:

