Results in deathIs immediately life-threateningRequires in-patient hospitalization or prolongation of existing hospitalizationResults in persistent or significant disability or incapacityResults in a congenital abnormality or birth defectIs an important medical event that may jeopardize the patient or may require medical or surgical intervention to prevent one of the outcomes listed above

All SAEs starting from enrolment until the last contact with the participant, whether or not they are related to the study product, will be reported.

AEs and SAEs during the trial will be reported in future publications. Harms will be coded in accordance with MedDRA at time of safety outcome reporting. Summary of symptom-based AE, SAE, and death reports observed during the studies will be reviewed by the trial DSMB at predetermined checks (quarterly). The AE/SAE will be labelled “Probable,” “Possible,” “Plausible,” or “Unlikely” due to SR. Summary statistics of AEs/SAEs, including mean, minimum, and maximum frequencies and percentages across clusters among enrolled subjects, will be provided by treatment arm. Statistical comparisons of the AE/SAE rates between the two arms will be conducted upon the completion of the study. Two sets of statistical analysis will be run. One set will compare the proportion of having at least one occurrence in each symptom-based AE/SAE during the whole study between the two arms, and the other will compare the total number of occurrences for each AE/SAE between the two study arms. If the data collected permits meaningful statistical hypothesis testing, *p*-values from the treatment comparisons will be reported, with multiplicity correction via the FDR approach [44].

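### Read literally, the between-arm adverse event comparison admits events from the 4-month baseline before any product is deployed, and nothing in the protocol excludes them

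*Protocol article*

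**What the plan says.** Outcomes {12} lists adverse events (AEs) and serious adverse events (SAEs) "as measured by solicited and unsolicited reports during baseline and intervention phase". Its next sentence says that their frequencies and percentages "across clusters among enrolled subjects will be summarized by treatment arm".

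Adverse event reporting and harms {22} plans two between-arm analyses. One compares the proportion "having at least one occurrence in each symptom-based AE/SAE during the whole study between the two arms"; "the other will compare the total number of occurrences for each AE/SAE between the two study arms". The same section adds: "All SAEs starting from enrolment until the last contact with the participant, whether or not they are related to the study product, will be reported".

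On timing, Cohort follow-up states: "Children enrolled in the baseline cohort will be followed for a 4-month period, prior to the distribution of the study products". It gives the total follow-up as 28 months, 4 of baseline and 24 after deployment. Trial design {8} describes the two intervention cohorts as "each followed for 12 months for a total of a 24-month follow-up with intervention". Cohort follow-up also says that households in the buffer zone receive neither product, and that baseline children may enrol again in cohort 1 or 2.

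**The concern.** An event before deployment cannot be caused by the product. If such events enter the comparison, they add roughly the same number to each arm and pull both the ratio and the difference towards no effect. In a safety analysis that error runs in the wrong direction: a real harm becomes harder to see.

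The stated window has two further weaknesses. A single proportion with at least one event would mix children observed for 4 months with children observed for 12. And because baseline children may enrol again, an event before exposure could mark a later-exposed child as a case.

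**Working it through.** **The plan's own figure.** Table 1 gives 60 clusters × (20 + 14) children = 2040 per cohort. Three cohorts give 6120, which matches the Abstract. The protocol states no AE rate, power or sample size for the safety comparison, so all AE rates and effects below are assumptions.

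**Share of baseline in core areas** (Table 1; no loss to follow-up):
- Child-months: baseline 1200 × 4 = 4800; intervention 2 × 840 × 12 = 20,160. Share 4800 / 24,960 = 19.2%.
- In child-years: 400 and 1680, total 2080.
- Records: 1200 / (1200 + 1680) = 1200 / 2880 = 41.7%.

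**Rate (count) ratio if pooled.** With equal background rates in both arms, the pooled ratio is (1680 × RR + 400) / 2080.

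| True RR | Pooled RR | Reduction in log ratio |
|---|---|---|
| 1.25 | 1.20 | 18% |
| 1.5 | 1.40 | 16% |
| 2.0 | 1.81 | 15% |
| 3.0 | 2.62 | 12% |

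**At least one event.** Per arm there are 840 intervention children (risk 1 − exp(−rate × 1 year)) and 600 baseline children (risk 1 − exp(−rate / 3)). The baseline term is the same in both arms, so the risk difference is multiplied by 840 / 1440 = 0.583, a cut of 41.7% at any rate. Power below is two-sided at 5%, ignoring clustering and the multiplicity correction.
- Rate 0.2 per child-year, RR 2.0: risks 0.181 and 0.330. The risk ratio goes from 1.82 to 1.65 and the risk difference from 14.8 to 8.7 points.
- Rate 0.2, RR 1.5: risk ratio 1.43 to 1.34; risk difference 7.8 to 4.5 points; power 0.97 to 0.92.
- Rate 0.05, RR 1.5: risk ratio 1.48 to 1.39; power 0.52 to 0.45.

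**How far the 42% depends on re-enrolment.** It treats every baseline record as a separate child. At the other extreme, suppose all 600 baseline children per arm are among the 840 and each child counts once. The multiplier is then (600 × exp(−rate / 3) + 240) / 840. At a rate of 0.2 this is (600 × 0.9355 + 240) / 840 = 0.954, a cut of about 5%. The rate-ratio results do not depend on overlap.

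**Buffer zone, for scale.** Intervention child-years are 1680 core and 2 × 1200 = 2400 buffer. If all enrolled children were included, a core RR of 1.5 would become (1680 × 1.5 + 2400) / 4080 = 1.21 without any baseline time. Adding all 680 baseline child-years (400 core + 840 × 4 / 12 = 280 buffer) gives (1680 × 1.5 + 2400 + 680) / 4760 = 1.18.

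**The case against.** The strongest reply is that the protocol nowhere says that baseline events are pooled.
- The phase wording in Outcomes {12} may be a collection window only. Insecticide resistance carries the same wording there, and the section on entomological endpoints summarises it at baseline and by intervention year separately.
- Sample size {14} and the data sharing policy speak of a two-year study, which fits the 24 months with intervention.
- Clusters are allocated only during baseline, so an arm has no treatment meaning before deployment.
- The intention-to-treat definition requires a household that received product.
- A safety population is commonly left to the analysis plan.

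Most of this stands as far as it goes: a reader might infer that pooling is an explicit rule, and the documents do not support that. But the protocol does state a window, and usage is mixed. The participant timeline puts baseline inside the study period, Cohort follow-up counts it in the 28 months, and Outcomes {12} names baseline and then summarises by arm. The intention-to-treat rule is stated for the primary and secondary objectives, none of which is safety. An analyst following the text could include baseline without departing from it.

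A reader might also infer that reporting differs materially between phases. It does not: visits follow the same schedule in all three cohorts, and AEs are solicited at them every 2 weeks. What product deployment adds is optional, in that "we may also collect unsolicited reports during compound visits and/or product replacement", or concerns other household members, who are outside a summary of enrolled subjects. This is at most a minor point.

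**Conclusion.** The point holds as a defect of wording with a real consequence if followed literally: pre-product events are admitted to the between-arm safety comparison and nothing excludes them.

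The dilution is moderate on the ratio scale: the log rate ratio is 12% to 18% smaller for true ratios of 1.25 to 3.0. The absolute difference in proportions can lose more, up to about 42% with no re-enrolment and much less with heavy re-enrolment at the assumed rate of 0.2. These figures assume planned numbers, equal background rates in both arms and phases, and no loss to follow-up; the true ratios and, for the proportions, the AE rates are assumed too.

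It would be too strong to say that a harm signal would be lost. At a rate of 0.2 and a ratio of 1.5, unclustered power is still 0.92. The loss matters most for uncommon events, where power is limited anyway. The calculation also shows that untreated buffer-zone children would dilute the contrast more than baseline does, so correcting the time window alone would not be enough.

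**What to change.** In Outcomes {12} and Adverse event reporting and harms {22}, state that between-arm AE/SAE summaries and tests use events with onset after product deployment, in cohort 1 and 2 children from core-area households that receive product (active or placebo). Use child-time at risk for the count comparison. Report baseline-phase and buffer-zone AEs separately as background. Collection and SAE reporting from enrolment stay as they are.

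This needs no new data. The comparison will contain fewer events, but the events removed are from children not exposed to either product in their homes and do not inform its direct harm.

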### Frequency and plans for auditing trial conduct {23}

An independent clinical research organization, fhiClinical, will hold the responsibility of conducting clinical monitoring at the protocol implementation level, ensuring that subjects are properly consented, data are appropriately gathered, safety events are documented and reported as required, investigational product is stored, distributed and collected per specifications, and that study close-out activities occur on a timely basis.

### Plans for communicating important protocol amendments to relevant parties (e.g., trial participants, ethical committees) {25}

Protocol amendments will be submitted to the study Sponsor and local IRBs and the WHO Ethical Review Committee (ERC) for approvals. Any amendments, outcomes, analyses, or more will be communicated in person and virtually. Face-to-Face meetings will be held between Lead PI, scientific director, and site staff. Additional attendees will include the National Malaria Control Program, MOH, and other in-country public health officials. In-country meetings will also be convened with civil society members, religious leaders, and key beneficiaries. These meetings will be critical as the trial progresses and the topics addressed will be pertinent to further execution of the trial. Due to the project design and geographic location of study team, teleconferences will be another method of formal project communication. Stakeholder teleconferences will be scheduled as needed to review and assess study progress and issues. Teleconference agendas will be drafted and distributed by UND.

### Dissemination plans {31a}

The plan for dissemination of results includes submission to WHO/VCAG, workshop with study partners, on-site meetings in Kenya, and presentations at scientific meetings and/or peer-reviewed publications.

## Discussion

ITNs and indoor residual spraying have contributed to substantial reductions in malaria burden since 2000 [1]. However, malaria remains a serious public health concern, particularly in sub-Saharan Africa due to gaps in protection from ITNs and IRS. Supplemental tools such as SRs may address these gaps in coverage and contribute to further reductions in malaria burden [5, 7, 45].

SRs, like the Mosquito Shield™, are devices containing volatile chemicals that disperse in air under ambient conditions (no requirement of electricity or heat to volatilize); they can be placed inside or around houses. The volatile chemicals introduced into the air repel mosquitoes from entering the treated space and/or disrupt mosquito biting and feeding habits, possibly impacting their survival and reproductive behavior [5]. SR products are envisioned to complement and enhance existing vector control methods due to the continual release of volatile AI which precludes the requirement of mosquito contact with a treated surface.

The role for SR products in malaria public health vector control are likely to be greatest in settings where early-evening and/or outdoor biting by *Anopheles* mosquitoes avoids the effects of ITNs and IRS. In addition, SR product chemicals operate through a different mode of action and laboratory assays have demonstrated behavioral effects against both insecticide susceptible and resistant anopheline and mosquito vectors responsible for transmitting multiple human pathogens [27]. Thus, SRs may serve as a tool in areas where insecticide resistance limits the effectiveness of ITNs and IRS. SRs may also reduce selection pressure for insecticide resistance and thereby maintaining the tools’ natural life span [7].

There are thousands of registered SR products already on the market and used for protection from nuisance biting. Current registered products include sophisticated, expensive products used in the USA and Europe (liquid vaporizers) as well as inexpensive and simpler products (e.g., mosquito coils) that are widely used throughout Africa and Asia. However, there is presently no public sector use of mosquito coils (or any other SR product format) for disease control due to insufficient evidence for WHO policy recommendation.

Over the past decade, formal national and international meetings have been convened to bring together academics, industry, funders, and global public health experts, including representatives from the WHO, to discuss the role of SR products in the reduction of arthropod-borne diseases. A critical aspect of these meetings and subsequent efforts has been to establish a critical path of development for SR products based on expert advice. This includes measures related to scientific, regulatory, and social parameters. In part, these criteria outline the endpoints of a target product profile (i.e., optimum product characteristics) for SR products. A SR vector control product class is currently under WHO assessment for public health value. However, the biggest evidence gap at the moment is the lack of sufficient epidemiological data needed to demonstrate public health impact across a range of eco-epidemiological settings to inform a potential WHO policy recommendation for the incorporation of SR products into current disease control programs. In 2017, the WHO VCAG recommended additional clinical trials to evaluate SR against malaria in Africa [46]. These knowledge gaps must be addressed to inform WHO SR policy recommendation. Once/if the WHO VCAG endorses a policy recommendation for the SR class to be recommended for public health use, national disease control programs will have the option of adopting a SR policy and “next-in-kind” SRs (e.g., with active ingredients to include other volatile pyrethroids such as metofluthrin) will have the opportunity to be marketed within the public health channel without the need to undergo WHO VCAG assessment, incentivizing SR product research.

This trial will generate evidence to support decision-making by WHO to recommend SR products for public health use and inform considerations of a national policy to include SRs in vector-borne disease control programs. Outputs will align with those of other global health stakeholders addressing residual malaria transmission, insecticide resistance, and access and barriers to market introduction of new vector control products. If the SR product is effective, it may be deployed in malarious areas to complement other vector control interventions such as ITNs to help mitigate the problems of insecticide resistance and/or vector biting at time where ITNs may be ineffective to further drive malaria towards elimination.

